## Abstract

**Background:**

Traditional Chinese medicine (TCM) is a widely applied complementary therapy for cancer patients. It can reduce the chemical drugs induced toxic effects to improve the quality of life (QOL). This study applies the highest quality of clinical trial methodology to examine the role of TCM in improving QOL of postoperative non-small-cell lung cancer patients.

**Methods and design:**

This study is a multi-center, randomized, placebo-controlled, double-blind trial. Four hundred eighty patients will be recruited into seven different research centers in China. These patients that meet the inclusion criteria will be randomized into either a treatment group or a placebo group. Each group will receive treatments of 3-weekly chemotherapy with TCM or placebo for four cycles. The primary outcome will involve the evaluation of QOL and the secondary outcome assessments will include two-year disease-free survival rate and disease-free survival. Other efficacy assessments are changes of TCM symptoms and toxicity. Side effects and safety profile of the therapy would be evaluated at the same time. The investigators expect that TCM therapy combined with chemotherapy is superior to chemotherapy solely in terms of QOL improvement and disease-free survival extension. "Intention-to-treat" analysis will include all randomized participants.

**Discussion:**

The results from the clinical trial will provide evidence for the effectiveness of chemotherapy combined with or without TCM in QOL of postoperative NSCLC patients.

**Trial registration:**

Clinical Trials.gov (Identifier: NCT01441752).

## Background

Lung cancer is one of the most common malignant tumors in the world, accounting for 26–29% of all cancer deaths [1]. Increasingly, lung cancer is becoming a global health problem, with greater than 1 million deaths annually attributed to lung cancer [2]. Non-small cell lung cancer (NSCLC) accounts for approximately 80% of all lung cancer diagnoses and more than 75% of the patients are diagnosed at an advanced stage. Consequently, the prognosis for NSCLC continues to remain poor, with a 5-year survival of 15% [3].

At present, the high rate of recurrence and metastasis of postoperative non-small cell lung cancer (NSCLC) patients is one of the leading causes resulting in failure of treating lung cancer. More than 35% of postoperative lung cancer patients with stage I died in 5 years due to recurrence or metastasis; the 5-year survival rate of stage II, IIIa, IIIb was 31%, 17.9% and 11.7% respectively. The survival rate was improved by 5% with adjuvant chemotherapy after resection, so regimen consist of platinum-based two chemical medicines are commended as the adjuvant chemotherapy for treating postoperative NSCLC patients, but the toxicity and side effects of chemotherapy such as nausea and vomiting, hair loss, and bone-marrow depression can decrease quality of life (QOL) of patients [4-6]. These adverse reactions need to be treated, otherwise which will impact the completion of treatment. Literature and preliminary studies have shown that traditional Chinese medicine (TCM) can prolong survival and improve QOL, but high-level evidence is desperately needed to support this finding [7].

Over the past 10 years, many oncologists focused on survival advantage of adjuvant chemotherapy of postoperative non-small cell lung cancer patients. Data from JBR.10 study showed that overall QOL and functional domain scores are somewhat compromised after thoracotomy and pneumonectomy; but scores improve fairly early in patients who are not receiving chemotherapy [8]. As expected, adjuvant chemotherapy has an immediate negative impact on a number of aspects of QOL in individuals with NSCLC who have undergone resection with curative intent [9]. Chief among these is the symptoms that reflect most of the serious adverse effects associated with platinum-based chemotherapy: fatigue, loss of appetite, nausea, and vomiting. Therefore, QOL in clinical assessment has become more and more prominent in clinical research [10].

Over the past decade, Chinese medicine has made progress in the treatment of lung cancer patients. Chinese medicine has some unique advantages over chemical drugs, such as improving the quality of life, reducing recurrence rate and prolonging overall survival, etc. Regarding KPS score, traditional Chinese medicine can stabilize and improve the KPS scores after surgery in 82.0% to 90% patients [11,12]. In addition, it can improve QOL significantly by using NCI-L evaluation. 85% to 87.5% of postoperative patients can stabilize and improve the body weight after receiving TCM therapy [11-15]. Two comparative studies from Japan indicated Chinese herbal medicine to be effective in reduction of chemotherapy-induced muscle pain and diarrhea [16,17].

[name] in Longhua hospital affiliated to Shanghai university of TCM has been doing clinical research on advanced lung cancer patients since the 1960s. His team have completed four prospective randomized clinical studies supported by China's State Science and Technology. The result showed that disease stable rate was 67.83%, 1, 3 and 5-year survival rate was 60.94%, 31.86% and 24.22% respectively in the treatment group. Median survival was 417 days (13.9 months). The immune function and QOL were improved after treated with combined Chinese and Western medicine compared to the control group [18-25]. This reflected characteristics and therapeutic effect of Chinese medicine on treatment of lung cancer based on syndrome differentiation. But these studies have methodological issues and can’t be widely accepted worldwide.

This paper has been compiled to outline the methodology for a randomized-controlled clinical study the effect of chemotherapy combined with or without TCM in QOL of postoperative NSCLC patients that adhere to the CONSORT [26] checklist in its design.

### Study aims

The primary aim of this study is to evaluate the effectiveness of chemotherapy combined with or without TCM in QOL of postoperative NSCLC patients. The secondary aims are to compare the disease-free survival time (DFS), two-year disease-free survival rate and safety of intervention in the two groups.

## Methods

### Study design

This study is a multi-centered, randomized, placebo-controlled, double-blind trial. Subjects from seven clinical research centers in China will engage into the trial. Longhua hospital affiliated to Shanghai university of TCM, Shanghai Chest Hospital affiliated to Shanghai Jiao Tong University, Ruijin Hospital affiliated to Shanghai Jiao Tong University, Huadong hospital affiliated to Fudan university, NO.6 people’s hospital affiliated to Shanghai Jiaotong university and Changzheng Hospital of the Second Military Medical University. Eligible participants will be randomly allocated into either of the two groups (chemotherapy with TCM or chemotherapy with placebo) and will receive treatment for 4 cycles (Figure 1).

**Figure 1 F1:**
[figure not shown]
Flow diagram of the study.

### Randomization

Dynamic stratified and randomized method is applied in this study. Random numbers will be automatically generated by computer referring to pre-configured stratified factors (stages, pathological types, ages and TCM syndromes). Shanghai Clinical Research Center will provide the random number to each participating center. The block size and treatment-assignment table will not be available to the researchers until the end of the study.

### Target population and selection

NSCLC patients received complete resection with confirmed pathological diagnosis of stage Ib-IIIa; TCM syndromes are Yin deficiency, Qi deficiency, Qi and Yin deficiency, Spleen and Kidney deficiency.

### Diagnostic criteria

Diagnostic criteria for primary bronchial lung cancer: According to the "New compiled diagnosis and treatment norms of common malignant tumors" (Volume IX - primary bronchial lung cancer, the Chinese Anti-Cancer Association compiled, Beijing: Chinese Union Medical University Press, 1997: 737–781).

TNM stage of primary bronchial lung cancer: According to the staging system of 2009 International Union Against Cancer (UICC), version 7.

### Syndrome differentiation criteria

Syndrome differentiation criteria based on "The Guiding Principles of Clinical Research of New Chinese Medicine (trial)" (China Pharmaceutical Technology Publishing House, 2002) and "Shanghai diagnosis and treatment routine of TCM Syndrome"(Shanghai Municipal Health Bureau edit). Four syndromes of TCM are set as follows:

Qi deficiency syndrome is composed of the following symptoms: coughing, phlegm, poor appetite, spiritlessness and weakness, light and plump tongue; secondary symptoms of spontaneous sweating, loose stool or soft slippery pulse.

Yin deficiency syndrome contains main symptoms of coughing, less phlegm, dry mouth, red tongue; secondary symptoms of the night sweating, heartburn and insomnia, low fever, thread and rapid pulse.

Qi and Yin deficiency syndrome contains main symptoms of coughing, less phlegm, shortness of breath, spiritlessness and weakness, thirst without the desire to drink; secondary symptoms of spontaneous sweating, night sweating, reddish tongue or tongue with teeth marks, and thread and weak pulse.

Spleen and Kidney deficiency syndrome contains main symptoms of coughing, shortness of breath, dyspnea after movements, weakly coughing; secondary symptoms of soreness of loins, tinnitus, loose stool, spiritlessness and weakness, light tongue or tongue with teeth marks, and deep thready and weak pulse.

The diagnosis can be given with the conditions of at least two of the main symptoms and one of the secondary symptoms.

### Inclusion criteria

Meet the diagnostic criteria of primary bronchial lung cancer, and pathologically or cytologically confirmed of squamouscarcinoma, adenocarcinoma, adenosquamous carcinoma or large cell carcinoma of the lung, age between 18 and 75 years old; TCM syndromes are Yin deficiency, Qi deficiency, Qi and Yin deficiency or Spleen and Kidney deficiency, Eastern Cooperative Oncology Group (ECOG) performance status of two or less, Stage Ib ~ IIIa with complete resection, first chemotherapy treatment within 6 weeks after operation, normal hematological function with total neutrophil count >1.5 × 10^9^/l and platelets >80 × 10^9^/l, normal liver function and kidney function, voluntarily involved to clinical study and sign informed consent.

### Exclusion criteria

Suffering from other primary malignant tumors; incomplete resection or uncertain to take resection; serious problem of heart, liver or kidney with severe dysfunction; being pregnant or breast-feeding, mental or cognitive disorders that would influence judgment of QOL in this study; during the period of adjuvant chemotherapy, or prior chemotherapy; being participating other drug trials; allergy to the drug in the study. Any patient with problems mentioned above will be excluded from this clinical study.

### Sample size

Refer to the results of JRB.10 study, for early lung cancer patients after three-month adjuvant chemotherapy, the QOL score assessed by QLQ-C30 scale decreased 27% compared with baseline. The sample size of this study is based on the validity of assumptions and clinical experience of the past. Compared to the baseline, it is estimated that the QOL score assessed by QLQ-C30 scale for patients treated with three-month postoperative adjuvant chemotherapy, there was 15% of patients with no deterioration of QOL combined with TCM than treatment without TCM. Inspection level α = 0.05, grasp 1-beta = 0.90, compared with the baseline, the QOL score assessed by QLQ-C30 scale after three-months in the treatment group decline 12% while 27% in the control group, made 198 cases of sample size in each group and consider 20% off rate, it is expected that the research team observed 480 cases (n = 240 cases) of patients in 2 years to compare QOL of postoperative NSCLC patients by chemotherapy with or without TCM.

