### Primary outcome measurement

#### Quality of life

Quality of life scale: QLQ-LC43 scales made by EORTC will be applied to assess the quality of life of patients. Scoring method is used to assess the results according to the score changes [27]. Scores of general QOL and each field is calculated respectively by international uniform scoring system prior and after intervention. Performance status of patients physical conditions are assessed according to ECOG PS standard before and after each treatment.

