### Statistical analysis

All the clinical data will be saved in computers after collection work and database will be set up by Microsoft Access 2007 software. Statistical analysis will be conducted on an intention-to-treat basis with a 95% confidence interval using the SPSS 16.0 statistical package. For analysis of baseline characteristics, either two-sample t tests or Wilcoxon rank sum tests for continuous data and Chi-squared tests or Fisher’s exact tests for categorical data will be conducted after the test for normality. Kaplan-Meier survival analyses should be used for calculating median survival time (MST), Long-Rank is used between two groups. A significance level of 5% will be used throughout the analysis. Experts of Shanghai Medical Clinical Research Centre will be invited to manage the statistic analysis.

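### The planned effect is stated both as a fall in score and as a share of patients, and 198 per group at 90% power follows from neither

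*Protocol article*

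**What the plan says.** The Sample size section gives the planning effect in two forms.

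- **As a score.** For the earlier adjuvant chemotherapy trial it says "the QOL score assessed by QLQ-C30 scale decreased 27% compared with baseline". The assumption for this trial is worded the same way: "after three-months in the treatment group decline 12% while 27% in the control group".
- **As a share of patients.** Between those two statements, the expected benefit reads "there was 15% of patients with no deterioration of QOL combined with TCM than treatment without TCM".

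The error rates are "Inspection level α = 0.05, grasp 1-beta = 0.90". The result is 198 per group, raised to 240 per group (480 in all) for 20% loss. The section gives no SD, baseline mean or formula.

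Under Primary outcome measurement, Quality of life, the scale is named differently: "QLQ-LC43 scales made by EORTC will be applied to assess the quality of life of patients". On how results are judged, it says "Scoring method is used to assess the results according to the score changes", with a citation for the method.

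**The concern.** A score that falls by 27% on average and 27% of patients getting worse are different quantities. They have different variances, call for different tests and lead to different sample sizes. A mean fall of 27% could arise from very different proportions of patients deteriorating, so one figure cannot be converted into the other without the distribution of the changes.

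Quality of life is the primary aim, so the 90% power statement is what a reader will use to interpret the result, especially a null one. If that statement is not tied to a defined variable, nobody can say what difference the trial was built to detect. The loss allowance adds a smaller problem: the number expected to remain is below the number the section says is needed.

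**Working it through.** **Inputs from the Sample size section:** alpha 0.05; power 0.90; 12% v 27%; 198 per group; 20% loss; 240 per group. Sidedness is not stated (the Statistical analysis section says only "A significance level of 5% will be used throughout the analysis"), so two-sided is assumed, with z = 1.96 and 1.2816. One-sided results are also given.

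**1. Trying to reproduce 198 as a comparison of proportions.**

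n = [1.96·√(2·p̄(1−p̄)) + 1.2816·√(p1(1−p1) + p2(1−p2))]² / (p1−p2)², with p1 = 0.27, p2 = 0.12, p̄ = 0.195.

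- First term: 1.96 × √0.31395 = 1.098
- Second term: 1.2816 × √(0.1971 + 0.1056) = 0.705
- n = (1.803)² / 0.0225 ≈ 144.5, so 145 per group

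| Variant | n per group |
|---|---|
| Two-sided | 145 |
| Two-sided, continuity correction | 158 |
| Two-sided, unpooled variance | about 141 |
| Two-sided, arcsine | about 142 |
| One-sided | 118 |
| One-sided, continuity correction | 131 |

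None is close to 198. In the other direction, two-sided power at n per group is Φ[(0.15√n − 1.098)/0.550]:

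- n = 198: Φ(1.84) ≈ 97%
- n = 192: Φ(1.78) ≈ 96%

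**2. Trying to reproduce 198 as a mean score change.**

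n = 2(1.96 + 1.2816)²·SD²/d². Neither SD nor d in points can be filled in from the document, so 198 cannot be checked. What can be said is the standardised difference detectable at 90% power, 3.2416·√(2/n):

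- n = 198: 0.326 SD
- n = 192: 0.331 SD

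At 192 per group that is 6.6, 8.3 or 9.9 points for an assumed SD of 20, 25 or 30.

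To see how far the answer depends on the missing figures, take d as 15% of an assumed baseline score. The table gives n per group for 90% power, two-sided:

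| Assumed baseline | d (points) | SD 20 | SD 25 | SD 30 |
|---|---|---|---|---|
| 55 | 8.25 | 124 | 193 | 278 |
| 65 | 9.75 | 89 | 139 | 199 |
| 75 | 11.25 | 67 | 104 | 150 |

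With 192 per group, power runs from 77% (baseline 55, SD 30) to over 99%. Only that one cell of nine is clearly below 90%; the cells needing 193 and 199 have about 90% and 89%.

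**3. The loss allowance.**

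- 198 / (1 − 0.20) = 247.5, so 248 per group (496 in all)
- 198 × 1.20 = 237.6, so 238, close to the stated 240
- 240 × 0.80 = 192, which is 6 fewer than 198

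The 240 is what results from adding 20% and rounding up. Dividing by 0.80 gives 248.

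**The case against.** The strongest defence is that a journal article condenses the full protocol. An SD may have been used and left out, and the primary outcome section refers its scoring method to a cited source. Judging results by score changes could mean comparing mean changes, or classing each patient as better, stable or worse. This stands, and it limits what can be said about how 198 was obtained. It does not remove the conflict inside the Sample size section, where one effect is stated in two units.

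Some stronger readings are tempting and are not supported:

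- **That the 90% power belongs to a responder comparison.** The sentence about patients and the absence of an SD suggest it, but the arithmetic does not bear it out: 12% v 27% needs about 145 per group. Other pairs 15 points apart do land near 198 (20% v 35% with continuity correction gives 198), but those rates are not in the document.
- **That the trial is underpowered.** As proportions, 198 is more than enough. As a mean change, most of the assumed grid gives about 90% or more. The direction of any error is unknown.
- **That the outcome is measured on an unrelated instrument.** Two scale names are used, but the document does not say how they relate. That justifies asking for consistent naming and no more.
- **That the missing deterioration cut-off is itself a fault, or that analysts could choose their analysis later.** Such detail is commonly left to the full protocol or analysis plan, which are not shown.

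**Conclusion.** The point holds in this form. The Sample size section states its effect in two incompatible units, and its 198 per group at 90% power is reproduced on neither. As proportions the figure would be about 145 (158 with continuity correction), with about 97% power at 198. As a mean change it cannot be derived from what is given. The power statement is therefore not tied to the primary outcome that the article names. Separately, 20% loss from 240 leaves 192 per group, 6 short of the stated need.

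The proportion results rest on a two-sided 5% test; one-sided variants are further from 198. The score-change figures in points rest on assumed baselines and SDs and illustrate a range only. The 0.33 SD figure needs no such assumption beyond a two-sided comparison of means with equal groups.

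**What to change.** Choose one primary variable and use it, with one scale name, in both the Sample size and Quality of life sections. Either choice is acceptable: mean change in the general quality of life score, or the proportion of patients without deterioration. If the two scale names refer to related questionnaires, say how they relate.

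Then restate the power for that variable at 192 evaluable per group, keeping enrolment at 480:

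- **Mean change:** a detectable difference of about 0.33 SD at 90% power, turned into points with a justified SD (6.6, 8.3 or 9.9 points if the SD is 20, 25 or 30).
- **Proportion without deterioration:** about 96% power for 12% v 27%, provided those figures can be justified as shares of patients rather than falls in a score. If they cannot, recalculate from rates that can.

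Replace the 198 with the figure that the chosen calculation gives, state whether the test is two-sided, and describe the loss allowance so that it agrees with 192 remaining.

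The cost is some rewording and one recalculation. No extra patients or data collection are needed.

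### Read as a comparison of proportions, the stated inputs need 145 to 158 evaluable patients per arm, not 198; and 240 per arm does not deliver 198 after 20% loss

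*Protocol article*

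**What the plan says.** The whole calculation is in the Sample size section of the protocol article.

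- Error rates: "Inspection level α = 0.05, grasp 1-beta = 0.90". Sidedness is not given.
- Effect: QLQ-C30 quality of life after three months is expected to "in the treatment group decline 12% while 27% in the control group". The same effect is also described thus: "there was 15% of patients with no deterioration of QOL combined with TCM than treatment without TCM".
- Result and allowance for loss: these inputs "made 198 cases of sample size in each group and consider 20% off rate".
- Enrolment: "it is expected that the research team observed 480 cases (n = 240 cases) of patients in 2 years".

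As the sentence runs, 198 per arm is the number before loss, and 240 per arm is the number after allowing for it. The test and formula are not named.

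**The concern.** Inputs, result, loss rate and total are all printed, so the chain can be checked, and two of its links fail. First, a difference of 15 percentage points starting from 27% is fairly large, and 198 per arm looks too many for 90% power. Second, 240 is less than 198 divided by 0.8, so the enrolment target does not protect the number that it is meant to protect.

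This paragraph is the only numerical justification for the trial's size on its primary outcome. If its figures do not follow from one another, a reader cannot tell what power the trial has, how many evaluable patients it needs, or why 480 people are asked to take part.

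**Working it through.** **Inputs (Sample size section).** p1 = 0.27 (control), p2 = 0.12 (treatment), so d = 0.15 and the mean rate p = 0.195. Alpha 0.05, power 0.90, loss 20%, 1:1 allocation. Assumed: two-sided test (z = 1.960; for power, z = 1.282) and percentages that are proportions of patients. Using 73% and 88% without deterioration gives the same results.

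**Step 1: try to reproduce 198.**

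Pooled-variance formula: n = [1.960 × √(2p(1 − p)) + 1.282 × √(p1(1 − p1) + p2(1 − p2))]² / d²

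- √(2 × 0.195 × 0.805) = 0.5603, and 1.960 × 0.5603 = 1.0982
- √(0.1971 + 0.1056) = 0.5502, and 1.282 × 0.5502 = 0.7051
- n = (1.0982 + 0.7051)² / 0.0225 = 144.5, so **145 per arm**

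Continuity correction: n' = (n/4) × [1 + √(1 + 4/(n·d))]², which gives 157.6, so **158 per arm**.

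| Variant at 90% power | Per arm |
|---|---|
| Two-sided, pooled | 145 |
| Two-sided, continuity-corrected | 158 |
| Two-sided, unpooled variance | 142 |
| Two-sided, simple pooled variance | 147 |
| Two-sided, arcsine | 142 |
| Two-sided, Fisher exact | about 156 |
| One-sided, pooled | 118 |
| One-sided, continuity-corrected | 131 |

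None gives 198.

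**Step 2: where 198 might come from.** 158/0.8 = 197.5, which rounds up to 198. So 198 equals the corrected requirement with one 20% allowance included, provided that 157.6 is rounded up to 158 first.

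**Step 3: from 198 to 240.** This step does not depend on the endpoint scale.

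- 198/0.8 = 247.5, so 248 per arm would be needed to keep 198 after 20% loss.
- 198 × 1.2 = 237.6, close to the stated 240, which suggests multiplying by 1.2 rather than dividing by 0.8.
- 240 × 0.8 = 192, which is 6 per arm below 198.
- 240 per arm keeps 198 only if loss is at most 1 − 198/240 = 17.5%.

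**Step 4: power on the proportions reading (two-sided).**

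| Evaluable per arm | Uncorrected | Continuity-corrected |
|---|---|---|
| 192 | 96.3% | 95.1% |
| 198 | 96.7% | 95.6% |
| 240 | 98.7% | 98.3% |

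Fisher's exact test gives 95.5% at 192 and 96.0% at 198.

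**Step 5: enrolment for 90% power with one allowance.**

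- Corrected: 158/0.8 gives 198 per arm, 396 in total; 480 − 396 = **84** more than needed.
- Uncorrected: 145/0.8 = 181.25, so 182 per arm, 364 in total; 480 − 364 = **116** more than needed.

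**The case against.** **The percentages may be mean falls in score.** Most of the Sample size section speaks of a score that drops from baseline, and the Primary outcome measurement section describes score changes with no definition of a responder. Only the clause about patients without deterioration points to proportions. If means were intended, no SD is given and 198 can be neither confirmed nor refuted: it would imply an SD of 15 / [(1.960 + 1.282) × √(2/198)], about 46 percentage points. This stands, so the 145 to 158 figure is conditional on the proportions reading. It does not rescue the step from 198 to 240.

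**Double counting of the loss is not shown.** A reader might infer from 158/0.8 that the allowance was certainly applied twice. The match is striking, but the article shows no steps and presents 198 as the number before loss. There is also another route to 240: with continuity correction, 95% power needs 192 per arm, and 192/0.8 = 240. That route bypasses 198 and contradicts the stated 90% power, but it shows that the origin of the figures cannot be settled from the document.

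**The shortfall of 6 per arm is small.** True: on the proportions reading, 192 rather than 198 costs about half a percentage point of power. It matters as an inconsistency, not as a loss of information.

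**The error is on the safe side.** This also stands on the proportions reading. A larger trial does not bias the comparison, and it helps the disease-free survival outcomes.

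**An article condenses the protocol.** That would excuse an omitted formula. It does not excuse printed figures that disagree.

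**Conclusion.** Wrong as written, moderate severity. Two statements hold with different strength.

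- **Without any assumption about the endpoint:** 198 evaluable per arm, 20% loss and 240 enrolled per arm are not compatible.
- **If the comparison is of proportions:** the printed inputs need 145 evaluable per arm, or 158 corrected, and not 198. The trial would then be larger than its stated justification supports, by 84 or 116 patients depending on the formula, with 95% to 96% power at the planned loss.

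A reader might conclude that the trial is underpowered because 192 falls short of 198. On the proportions reading it is not, as power exceeds the stated 90%. Nor does the document establish a single excess figure, or that the loss was counted twice. The validity of the primary comparison is not threatened; what fails is the stated basis for the sample size.

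**What to change.** Rewrite the Sample size paragraph so that it:

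1. states whether the endpoint is the proportion of patients whose quality of life deteriorates or a mean change in score, and gives the SD if it is a mean;
2. names the test, the sidedness and the formula;
3. applies the 20% loss once, by dividing by 0.8;
4. uses the same formula for the required number and for the power.

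If the endpoint is a proportion, either of these is consistent:

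- 158 evaluable and 198 randomised per arm (396 in total), for 90% power with continuity correction; or
- 480 randomised, 192 evaluable per arm after 20% loss, with about 95% power (corrected) or 96% (uncorrected) for 12% against 27%.

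If it is a mean change, the calculation has to be redone from the stated SD.

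The cost is one paragraph. On the proportions reading no additional patients are needed, and keeping 480 is acceptable if the paragraph says what it buys.
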